### Sample size

The sample size was calculated from the expected differential ICER per preterm birth avoided between the two groups. In accordance with Briggs [22], the following hypothesis is stated: with an expected incremental rate of preterm birth of 1.3 % (4.3 % in the control group [23] and 3.0 % in the experimental group), an expected incremental cost of 230 euros (including cost of initial and following point-of-care tests and cost of treatments for 10 % of the women [24]), and an expected differential ICER at 22,500 euros corresponding to the avoided cost of a preterm birth before 37 weeks [25], with an 80 % statistical power and a threshold for statistical significance set at a *P* value of 0.05, and assuming that a potential 20 % of patients will be lost to follow-up, these calculations showed that 6,800 patients are needed (3,400 per group). Considering the potential of inclusion of each participating center, the inclusion duration will be planned over a 12-month period. The maximal period of participation for the included women is 12 months.

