### Cost-effectiveness analysis

Incremental cost-effectiveness ratios (ICER) will be used to compare the cost and effectiveness of the experimental strategy with usual care. The ICER is the ratio of the difference between groups in costs to the difference in effectiveness. The difference in effectiveness equals the number of preterm births averted and is calculated as the number of preterm births in the screening group minus the number of preterm births in the control group. Thus, the ICER provides information on the potential acceptability of the intervention for decision makers. The costs perspective taken in our economic analysis is that of the healthcare payer. The time horizon started from the first prenatal consultation before the 20 weeks of gestation and ended at 6-months of age or death. The healthcare costs included are those that are likely to differ across the intervention and control groups. In our study, these costs are those associated with: screening using the point-of-care procedure (quantitative molecular analysis), control vaginal swabs for positive women, antibiotic treatments, antenatal hospital admissions, physicians’ consultations, management of complications, as well as neonatal costs for full term infants and preterm infants. Unit costs for health service use will be estimated using data from the French National Hospital Database (Programme de médicalisation des systèmes d’information, PMSI) and the National Tariff. Treatment costs were obtained from the French register of pharmaceutical specialties, an online database of information on healthcare products. The cost of the POC analysis using quantitative real-time PCR (qPCR) will be calculated using micro-costing technique, which is particularly well suited to evaluating the cost of an emerging technique [27]. The volume of resources used will be determined by direct observation of each stage of each testing procedure. Fixed and variable costs will be included. All resources will be valued in 2015/2016 euros, and the 12-month trial means there is no requirement to apply discounting. As the cost of preterm birth differs significantly according to the gestational age at birth [28–30], we will attempt to address this issue by calculating an ICER for specific birth gestational ages. Probabilistic sensitivity analyses, using the non-parametric bootstrap method, will be carried out to generate mean expected ICERs and to determine whether uncertainty or variation in the data used affect the ICERs [31]. In addition, cost-effectiveness acceptability curves were constructed to represent decision uncertainty surrounding cost-effectiveness estimates [32].

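### The bootstrap is assigned all uncertainty in the data behind the ICER, but resampling women cannot vary the qPCR unit price or the tariffs

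*Protocol article*

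**What the plan says.** All references are to the protocol article.

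- **Method** (Cost-effectiveness analysis): "Probabilistic sensitivity analyses, using the non-parametric bootstrap method, will be carried out to generate mean expected ICERs".
- **Purpose** (same sentence): besides producing those averages, the bootstrap is meant "to determine whether uncertainty or variation in the data used affect the ICERs". The abstract's Methods/Design paragraph likewise names bootstrapping and acceptability curves as the way uncertainty will be handled.
- **Acceptability curve** (same section): "cost-effectiveness acceptability curves were constructed to represent decision uncertainty surrounding cost-effectiveness estimates".
- **Test price** (same section): the point-of-care qPCR cost "will be calculated using micro-costing technique, which is particularly well suited to evaluating the cost of an emerging technique". Resource volumes come from direct observation of the testing steps, and "Fixed and variable costs will be included".
- **Other prices** (same section): "Unit costs for health service use will be estimated using data from the French National Hospital Database" and the national tariff, with drug prices from a register.
- **Planning figures** (Sample size): preterm birth 4.3% versus 3.0%, "an expected incremental cost of 230 euros" that includes tests and treatments, and a reference value of 22,500 euros per preterm birth avoided.
- **Other robustness analyses** (Statistical analysis): a sensitivity analysis mentioned alongside multiple imputation, and a per-protocol analysis. Neither is said to vary a unit cost.

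**The concern.** A trial-based ICER combines two kinds of input. Outcomes and resource counts are observed on each woman. Unit costs come from outside the sample of women and are common to all of them. A bootstrap over women addresses the first kind. The second enters each replicate as the same constant, so the stated method falls short of the purpose given to it.

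The qPCR price deserves particular attention for three reasons:

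- Systematic testing takes place in the experimental arm only, so the price does not cancel between arms.
- The protocol itself describes the technique as emerging.
- The price includes fixed costs, so it depends on throughput. Table 3 describes two laboratories serving the trial, whereas the Discussion aims at routine use nationwide. Volume, and with it the unit price, may differ between the two settings.

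A decision maker reading the acceptability curve would see the probability of cost-effectiveness at one price, with nothing to show how it moves at another.

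**Working it through.** **Inputs.** From Sample size: preterm birth rates 0.043 and 0.030; incremental cost 230 euros; reference value 22,500 euros; 10% of women treated; 3,400 per group with 20% loss, so 3,400 × 0.8 = 2,720 evaluable per arm. From Interventions: three control swabs for positive women. Assumptions, not in the document: the coefficient of variation (CV) of the price, the share of the 230 euros that is test cost, and the patient-level cost SD.

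**1. Planned ICER.** The stated difference is reproduced: 0.043 − 0.030 = 0.013. Then 230 / 0.013 = 17,692 euros per preterm birth avoided.

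**2. Break-even.** 22,500 × 0.013 = 292.5 euros per woman, and 292.5 / 230 = 1.27, a rise of 27% in the whole incremental cost. The test share of the 230 euros is not given. If it is s, the test price must rise by 62.5 / (230 × s):

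- s = 100%: 27%
- s = 80%: 34%
- s = 60%: 45%

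**3. What a bootstrap over women can see.** Treat all 230 euros as test cost and assume 10% of women have three extra tests. Tests per woman then average 1 + 3 × 0.1 = 1.3, with SD 3 × √(0.1 × 0.9) = 0.9. The implied price is 230 / 1.3 = 176.9 euros. The sampling SD of mean test cost is 176.9 × 0.9 / √2,720 = 3.1 euros. With the price 30% higher the mean becomes 299 euros and the SD 4.0 euros. The spread stays tight around either mean and comes only from the number of tests.

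**4. Shift of the ICER and the curve with price.** The SE of the effect is √[(0.043 × 0.957 + 0.030 × 0.970) / 2,720] = 0.00508. In net benefit at 22,500 euros this is 22,500 × 0.00508 = 114 euros. Net benefit is 292.5 − cost, and P is the normal probability that it exceeds zero, with sampling error in the effect only:

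| Change in the 230 euros | ICER (euros) | Net benefit (euros) | P |
|---|---|---|---|
| −20% | 14,154 | 108.5 | 0.83 |
| none | 17,692 | 62.5 | 0.71 |
| +20% | 21,231 | 16.5 | 0.56 |
| +30% | 23,000 | −6.5 | 0.48 |

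Each 10 euros per woman moves the ICER by 10 / 0.013 = 769 euros. At a given effect, that slope does not depend on what else enters the incremental cost.

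**5. How much too narrow the curve would be.** Let the price vary with a CV of 10, 20 or 30%, applied to the whole 230 euros. The SE becomes √[114.3² + (230 × CV)²] = 117, 123 or 134 euros, a rise of 2, 8 or 17%. P moves from 0.708 to 0.704, 0.694 or 0.680. Adding an assumed patient-level cost SD of 3,000 euros gives a base SE of 140 euros, and the rise falls to 1, 5 or 11%.

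**The case against.** **This is a condensed article.** A full protocol or economic analysis plan may contain deterministic analyses of unit costs, and their ranges are commonly left to such a document. That stands: a reader might infer that no price analysis is planned at all, and the article does not support this. The point here is narrower. The article makes a positive statement of what the bootstrap will show, and the method cannot deliver all of it.

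**The data used may simply mean patient-level data.** On that reading the bootstrap does what is asked. The reading is possible, but the section has just described micro-costed and tariff prices as inputs, and the sentence does not exclude them. The micro-costing also rests on observation, and the text does not say whether those observations enter the resampling. Even if they did, resampling observed steps would not vary the volume over which fixed costs are spread.

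**Sampling error in the effect dominates.** This is correct. The 95% range of the effect is 0.013 ± 1.96 × 0.00508, about 0.3 to 2.3 percentage points. At a fixed 230 euros the ICER then runs from about 10,000 to 76,000 euros, far wider than the 14,154 to 23,000 euros produced by −20% to +30% in cost. A reader might infer that the test price is the least certain input, or that the curve will look far too certain. The document gives no uncertainty for the price, and step 5 shows the added width is modest.

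**The 230 euros is not the test price.** Also correct. A reader might infer that a 27% rise in the test price reverses the conclusion. It does not follow: treatment is in the 230 euros, the split is not given, and the trial's incremental cost will also count admissions and neonatal care. The 22,500 euros is a sample-size assumption, and the Cost-effectiveness analysis section sets no decision threshold.

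**Conclusion.** The point holds in limited form. In the cost-effectiveness section, the only stated method for ICER uncertainty cannot vary the unit costs, so the acceptability curve will show sampling uncertainty alone. This cannot be widened to say that the document contains only one sensitivity analysis, since Statistical analysis adds one for missing data and a per-protocol analysis.

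The understatement of width is probably modest, about 2 to 17% in the SE of net benefit at 2,720 per arm for an assumed price CV of 10 to 30%, and less once patient-level cost variance is added. The larger issue is the unshown dependence of the result on price. In the planning illustration, moving the incremental cost from −20% to +30% takes the ICER from 14,154 to 23,000 euros and the probability of cost-effectiveness at 22,500 euros from 0.83 to 0.48. Those figures use the whole 230 euros as a proxy for the test price, hold the effect at 1.3 points and leave out patient-level cost variance. They show the sensitivity and do not forecast the trial's ICER.

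**What to change.** - Describe the bootstrap as addressing sampling uncertainty, and reword the purpose given to it accordingly.
- Add one-way or scenario analyses of the qPCR unit cost, including trial versus routine test volume, and of the neonatal tariffs. A range of ±50% on the test price would cover the break-even points in step 2.
- Report the threshold test price at which the conclusion changes, against a stated reference value.
- Redraw the acceptability curve at the low and the high test price.

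If a full economic analysis plan already contains these analyses, only the rewording and a cross-reference are needed. The cost is a few extra runs of the same code, with no new data from the women. The downside is a less favourable statement of uncertainty.

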
### Ethical aspects, laws and regulations

The study will be conducted in accordance with the Helsinki declaration and the French laws and regulations (Code de la Santé Publique, article L.1121-1/Loi de Santé Publique n°2004-806 du 9 Août 2004 relative à la politique de santé publique et ses décrets d’application du 27 Août 2006) and the International Conference on Harmonization (ICH) E6 Guideline for Good Clinical Practice. Regulatory monitoring will be performed by the sponsor. French ethics committee and French drug and device regulation agency approved conduct of the AuTop study at all sites (registered number respectively: Comité de Protection des Personnes Sud Méditerranée, reference number 14.026 and Agence Nationale de Sécurité du Médicament, reference number 140500A-41). This trial was registered into the government clinical trials under the identifier number NCT02288832 (ClinicalTrials.gov). Written Informed consent will be obtained from all subjects before inclusion.

## Discussion

This is the first large randomized controlled trial assessing the cost-effectiveness of a screen-and-treat program of molecular flora vaginal anomalies during the first trimester in pregnant women with low risk of preterm birth. This study was designed specifically to inform healthcare decision making, in an international context where the diagnosis of BV in pregnant women and its subsequent management care are controversial [33–37]. Several reasons could be stressed to explain these diverging opinions.

Firstly, there was a real lack of accuracy of diagnostic tools at the time of some studies. Most of the studies cited earlier focused on the Nugent score, which has some limitations. It must be performed on a fresh swab, and any delay in transporting the swab makes the test difficult to perform, its scoring requires experienced microbiologists to ensure consistency, and some pathogens associated with BV are not identified by such a technique, in particular *A. vaginae* [9]. Recent studies have demonstrated that molecular biology techniques have both higher sensitivity and specificity for the diagnosis of BV [7, 9, 15, 16] compared to the Nugent score and can detect several bacterial series for BV.

The second point concerns the appropriateness of antibiotic treatment [13, 19]. The nature of the antibiotics (such as metronidazole or clindamycin, pro- or prebiotics) and their modes of administration (oral versus vaginal) vary considerably between existing studies. Few studies have controlled for treatment efficacy [38]. In addition, although the frequency of recurrences after antibiotic treatment is high (from 28 % to 50 %), depending on the nature of the treatment and the length of time from its intake [39], most of studies did not consider this risk of recurrence. In the present project, we propose to use azithromycin because of its effectiveness on *A. vaginae* and *G vaginalis* with a lifetime that allows us to reduce the treatment duration and to increase the adherence rate [40].

The third point concerns the delay between BV and treatment. In cases of late diagnosis, and therefore delayed treatment, BV has already been established and can lead to obstetrical complications involving preterm birth [41]. In this present study, we have considered that the point-of-care test will be an interesting approach to minimize the feedback of the vaginal swab to the practitioner in order to rapidly prescribe the antibiotic treatment in cases where tests are positive. In our trial, the short window for providing a diagnostic result also appears essential for minimizing the number of women lost to follow-up who may benefit from an early antibiotic treatment. Indeed, this rate of “lost to follow-up patients” is important in this disease where asymptomatic disease, anxiety and low socioeconomic status are clearly identified risk factors [9].

Finally, the gestational age at inclusion is the greatest limitation of previous published studies. Due to the lack of data concerning the early phase of pregnancy, the authors may have underestimated the effectiveness of a universal screen-and-treat program in reducing the rate of “very preterm birth” (28 to 32 weeks). These subdivisions into “very preterm” and “moderate” or “late preterm” (that is, 32 to less than 37 completed weeks of gestation) are important since decreasing gestational age is associated with increasing mortality, intensity of neonatal care required, and hence increasing costs [42].

The main purpose of AuTop trial is to support at a nationwide level the feasibility, acceptability, and cost-savings of a routine point-of-care molecular diagnosis at the first stage of pregnancy. Although it is well known that the consequences in terms of morbidity and mortality of preterm birth are important and entail a significant economic burden, several studies have demonstrated that a large share of the incremental cost per surviving preterm infant is represented by neonatal care [43, 44]. The average length of this neonatal care can vary from 3 days to 6 months for very preterm births (including potential immediate re-hospitalization, programmed consultations and bronchiolitis prevention measures). We then decided to focus on this time horizon for the cost-effectiveness analysis.

In Kiss et al. [23], the prevalence of BV was around 7 % in their study population (which included women without subjective complaints, that is, contractions, vaginal bleeding, or symptoms suggestive of vaginal infection, or women with multiple pregnancies), with less than 2.3 % having an obstetric history at inclusion. It is well known that the ethnic origin influences the prevalence of bacterial vaginosis in pregnancy. In Kiss’s RCT, the population was 98 % white ethnic origin. In our study population, we will expected less than 65 % for the white ethnic group, based on our previous RTC conducted in the same French centers [11]. Consequently, we think that a prevalence of BV of 10 % in a population with or without clinical symptoms of BV and well balanced in terms of ethnic origins is not so optimistic. Our hypothesis of a decrease in the rate of preterm births from 4.3 % to 3.0 % seems to be a small expected gain in the rate of preterm births avoided. In fact, a mean difference of 1.3 % is actually a very large difference for pregnant women and decision makers, and should be sufficient to prevent major healthcare expenditure. Decision analysis is particularly useful when the difference in outcomes between strategies is small, and can provide insight into the costs contributing to the public decision-making process.

Given the need for scientific evidence (in terms of both efficacy and economic) regarding bacterial vaginosis screening in a population with low-risk factors for preterm birth, our analysis should be useful for clinicians and other healthcare decision makers involved in managing care of pregnant women.

## Trial status

At the time of manuscript submission, the status of the trial is yet recruiting. The inclusion of participants started in March 2015.

## Abbreviations

AAP: American Academy of Pediatrics
ACOG: American Congress of Obstetricians and Gynecologists
ANSM: Agence Nationale de Sécurité du Médicament
AP-HM: Assistance Publique-Hôpitaux de Marseille
BV: bacterial vaginosis
CDC: Centre for Disease and Controls
CONSORT: Consolidated Standards of Reporting Trials
DNA: deoxyribonucleic acid
eCRF: electronic case report form
HAS: Haute Autorité en Santé - French National Authority for Health
ICER: incremental cost effectiveness ratio
ICH: International Conference on Harmonization
PCR: polymerase chain reaction
SPSS: Statistical Package for the Social Sciences
PMSI: Programme de médicalisation des systèmes d’information
RCT: randomized controlled trial
